5.3.11 Control group

Participants in the control group will receive the same leaflet as the intervention group which will give falls prevention advice. This leaflet will be sent to the participant in the post with their baseline questionnaire. Participants will continue whatever podiatry treatment they currently receive for the 12 months of the study and usual GP care.

Participants will be sent a site and group specific newsletter at three months and with their six month follow-up questionnaire to inform them about progress with the study.

5.3.12 Health economics

The economic analysis will be performed using individual patient level data from the REFORM trial. The analytical approach will take the form of cost-effectiveness and cost-utility analyses. The cost effectiveness approach will assess value for money in terms of per fall averted, and the cost utility analysis will assess cost per quality adjusted life year (QALY) gained. The perspective for both analyses will be that of the UK NHS and Personal Social Service [34] as well as that of the society. Discounting for the future cost and health benefit will not be included considering the time frame for the trial is 12 months after the randomisation. The year of pricing will be set as the mid year of the trial.

Health benefits associated with the treatments will be measured in terms of both estimates of the mean number of falls, corresponding to the main outcome of the trial, and mean QALYs, which is defined as a year lived with full health. The EQ-5D [35] will be used to elicit patient utility values at different points in time and used to calculate QALYs for each patient using the area under the curve. [36] These utility values are used as ‘quality adjustment’ for each patient’s survival time.

Mean within trial estimates of cost and health benefits will be estimated using the regression approach to allow for the correlation between costs and effects as well as adjusting for covariates. This analysis will also account for skewness and censoring associated with time to event and cost data [37] [38] [39]. The result will be presented as incremental cost effectiveness ratio (ICER) where the difference of mean cost estimates between two arms are divided by the different of mean health benefit between two arms.

The uncertainty surrounding the decision to accept a treatment as the most cost-effective will be explored in cost effectiveness acceptability curves (CEAC) [40] These curves depict the probability of accepting a treatment as being cost-effective for a large range of willingness to pay values for an extra unit of health benefit. Sensitivity analysis will be conducted to explore the impact of underlying assumptions of the model and the range of unit costs on the cost effectiveness results.

The main outcome of the trial, fall reduction, could be regarded as an intermediate outcome to achieve the final target - the reduction in fracture. However, due to the restriction in the length of follow-up, the long term effect, the decreasing number of fractures, might not be observed in the current trial. Therefore a further analysis here is to explore the possible long term impact of the trial assuming that a falls reduction should also lead to a fracture reduction.

A decision analytic model approach will be adopted to perform such a task. The perspective will be the UK NHS and Personal Social Service and time horizon for this analysis will be a life-time horizon. Life-time horizon refers to following up every single participant in a hypothetical cohort until the last participant dies. The hypothetical cohort will be constructed, based on the characteristics of the trial population, to estimate the QALY yield and cost saving of the long term effect of the intervention. The model parameters which are not collected in the trial will be extracted from the existing literature. The model outputs will be the estimated expected mean costs, effectiveness, and QALYs associated with each alternative treatment. Estimated total costs and outcomes will be discounted properly according to the latest guidance of health technology appraisal.

Uncertainty regarding cost-effectiveness will be evaluated using probabilistic sensitivity analysis, where inputs into the analysis are defined as probability distributions which reflect uncertainty. The uncertainty surrounding the decision to adopt a given treatment option as a cost-effective treatment as different levels of willingness to pay will be represented in acceptability curves. The impact of assumptions undertaken in the analysis regarding the evidence over parameters or relating to the decision model (such as extrapolation) will be evaluated in sensitivity analysis, if possible

5.3.13 Adverse events

Details of any adverse events reported to the York Trials Unit either directly by the participant or by a member of the research team at the recruiting site will be recorded using the appropriate adverse event form and will be stored in the participant’s records.

This study will record details of any serious adverse events (SAEs) that are required to be reported to the Research Ethics Committee (REC) under the current terms of the Standard Operating Procedures for RECs. Non-serious adverse events will not be recorded or reported for this study.

A Serious Adverse Event (SAE) is defined as any untoward occurrence that:

(a) Results in death;

(b) Is life threatening;

(c) Requires hospitalisation or prolongation of existing hospitalisation;

(d) Results in persistent or significant disability or incapacity;

(e) Consists of a congenital anomaly or birth defect; or

(f) Is otherwise considered medically significant by the investigator.

An event is defined as ‘related’ if the event was due to the administration of any research

procedure. Whereas an ‘unexpected event’ is defined as: a type of event not listed in the protocol as an expected occurrence.

In the context of this study, an occurrence of the type listed in (a) to (f) will be reported as an SAE only if:

- The event is suspected to be related to an aspect of the research procedures

(e.g. wearing the orthotic, undertaking the exercise programme, completion of follow-up questionnaires, participation in feasibility or qualitative sub-studies, telephone contact).

AND

- It is an unexpected occurrence.

Hospitalisations, disabling / incapacitating / life-threatening conditions, falls and deaths are expected in the study population due to the age of the cohort, they will therefore only be reported as SAEs if they appear to be related to an aspect of taking part in the study. Expected adverse events which are related to the intervention include: aches and pains in the lower limb for longer than 48 hours; fall; new callus/corn formation, blisters, ulcers; skin irritation/injury including pressure sores; soft tissue injury. If a participant or a member of the research team rings the York Trials Unit to notify the occurrence of an adverse event, or an adverse event is reported in information provided in the follow-up questionnaires, then the trial coordinator – or designated person if unavailable should be informed immediately by telephone, email or in person. The trial coordinator (or designated person) will inform the Chief Investigator (CI) or designated person, and two members of the Trial Management Group (TMG) who will jointly decide if the event should be reported to the main REC as an SAE. Related and unexpected SAEs will be reported to the main REC within 15 days of the CI becoming aware of the event. Details of the assessment will be recorded on an ‘adverse event review form’.

The occurrence of adverse events during the trial will be monitored by an independent Data Monitoring Ethics Committee (DMEC)/ Trial Steering Committee (TSC). The DMEC/TSC will immediately see all SAEs thought to be treatment related and they will see SAEs not thought to be treatment related by the Trial Management Group at the next scheduled meeting.

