Participants will be prescribed a 30 minute home based foot and ankle exercise programme which should be undertaken three times per week indefinitely. The exercises will be demonstrated by the podiatrist at the participant’s initial visit and will be supplemented by a DVD demonstrating the exercises and an illustrated explanatory booklet showing how to do them at home. The exercise programme which is aimed at stretching and strengthening the muscles of the foot and ankle is based on the programme developed by Spink MJ *et al [22]* and the routine exercises prescribed by podiatrists in the UK.

Participants will complete a questionnaire at 1, 3, 6 and 12 months after randomisation to collect data on compliance with the intervention including the exercise programme footwear advice and insole use, which will be returned to the YTU.

1. Falls prevention leaflet

Participants will receive a copy of the latest falls prevention advice leaflet produced by Age UK. The current version of this document is called “Staying steady. Improving your strength and balance”. This leaflet will be sent to the participant in the post with their baseline questionnaire.

Participants will be sent a site and group specific newsletter at three months and with their six month follow-up questionnaire to inform them about progress with the study. The intervention group’s newsletter will include a section about the foot and ankle exercises in order to aid compliance.

The podiatrist will book a second appointment in approximately two to four weeks time to allow participants sufficient time to purchase new shoes if required. At the second appointment the podiatrist will check the suitability of the new footwear, check that the orthotic device is fitted correctly, customising if necessary. The podiatrist will reinforce the exercise programme. They will ask the participant if they have experienced any adverse events since their last appointment and if they have experienced any problems after undertaking the exercise programme.

It is not anticipated that participants will require a third appointment, however, if participants experience any problems with their orthotic, they will contact the clinic directly to arrange further appointments as required.

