9.3 Funding

Research funding has been secured from the National Institute of Health Research – Health Technology Assessment programme (reference: 09/77/01)

The main cost implication for the NHS is podiatrist time. This is classed as a Service Support Cost. From 2008/2009 service support costs have been met via the UKCRN Clinical Research Network Portfolio. It is anticipated that service support costs for REFORM will be met via this route once it has been adopted as a portfolio study.

- 1. Independent Steering Committee

Due to the low risk nature of this trial, approval will be sought from the funders to set up one independent steering and monitoring committee to undertake the roles traditionally undertaken by the Trial Steering Committee (TSC) and Data Monitoring and Ethics Committee (DMEC). This committee will comprise of an independent chair who will be a clinician with expertise in falls prevention, a statistician, a podiatrist, the chief investigator and other study collaborators. The independent members of the committee will be allowed to see unblinded data, but unblinded data would not be reported to the other members of the research team. The role of this committee will include the review of all serious adverse events which are thought to be treatment related and unexpected. The committee will meet at least annually or more often as appropriate. If however, the funders do not agree to one overarching committee, separate TSC and DMEC will be set up. The TSC will include an independent chair and at least two other independent members, along with the chief investigator and the other study collaborators. The DMEC will comprise of an independent chair, a statistician and a podiatrist. Both committees will meet annually. The role of the DMEC will be to immediately see all serious adverse events which are thought to be treatment related and unexpected.

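### The adverse-event rules in Protocol 5.3.13 and the committee section conflict on what is recorded, what counts as a reported SAE, and what the committee sees

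*Protocol*

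**What the plan says.** Section 5.3.13 opens with a broad recording rule. "Details of any adverse events reported to the York Trials Unit either directly by the participant", or by site research staff, "will be recorded using the appropriate adverse event form". The next paragraph limits SAE recording to those that must go to the REC, and adds: "Non-serious adverse events will not be recorded or reported for this study".

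The section then defines an SAE by six criteria, (a) to (f), without reference to cause. Such an event is reported as an SAE only if it is both suspected to be related to the research procedures and unexpected. An event is unexpected when its type is absent from the protocol's list of expected ones; severity plays no part.

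Later in 5.3.13, hospital admissions, disabling or life-threatening conditions, falls and deaths are called expected at this age, and "they will therefore only be reported as SAEs if they appear to be related to an aspect of taking part in the study". A second list gives expected events related to the intervention: prolonged lower-limb aches, falls, callus or corns, blisters, ulcers, skin injury and soft tissue injury. The 15-day REC report covers related and unexpected SAEs.

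On oversight, 5.3.13 shows the DMEC/TSC all treatment-related SAEs at once, and "they will see SAEs not thought to be treatment related by the Trial Management Group at the next scheduled meeting". The Independent Steering Committee section (9.4 in the contents table) says that a DMEC, if set up separately, will "immediately see all serious adverse events which are thought to be treatment related and unexpected".

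**The concern.** Three different decisions (what to write down, what the monitoring committee sees, and what goes quickly to the REC) are run together, and the sentences give different answers for the same event. Trials unit staff have to apply them largely unaided: section 6.1 plans no site monitoring visits and relies mainly on participants' own reports of adverse events.

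Two groups of events are exposed. One is serious events judged related but of a listed type, such as a fall with fracture while exercising or an admission for an orthosis ulcer. The other is the intervention's own anticipated harms, most of which are not serious. If the narrower sentences are followed, the first group may not be reported as SAEs and the second may not be counted, so the frequency of blisters or prolonged aches could not be stated in the final report.

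**Working it through.** No arithmetic applies, and the plan states no figure on this point. The check takes three test events through each rule. One assumption is needed: the SAEs that must go to the REC are read as the related and unexpected ones, as the 15-day sentence in 5.3.13 implies. The REC procedures it cites are not part of the document.

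**Event A: a serious fall judged related to the orthosis or the exercises**

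| Rule | Outcome |
| --- | --- |
| 5.3.13, related-and-unexpected test | Related, but falls are a listed type: not reported as an SAE |
| 5.3.13, sentence on events expected at this age | Expected but related: reported as an SAE |
| 5.3.13, 15-day REC report | Not unexpected: no 15-day report |
| 5.3.13, DMEC/TSC view | Treatment-related SAE: seen immediately |
| Independent Steering Committee section, separate DMEC | Not unexpected: outside the set seen immediately |

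The first two rows are opposite answers to one question. The last two differ on the committee's immediate view. Related deaths, admissions, and disabling or life-threatening conditions behave in the same way.

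**Event B: an unrelated hospital admission**

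- By definition it is an SAE under criterion (c).
- The sentence limiting SAE recording to REC-reportable events does not cover it.
- The committee is nevertheless to see it at its next scheduled meeting.
- The opening paragraph of 5.3.13 would have it recorded if it is notified, but that paragraph does not sit with the narrower sentence that follows it.

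**Event C: a blister telephoned in to the trials unit**

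- Opening paragraph of 5.3.13: recorded on a form.
- Next paragraph: not recorded.
- Blisters are on the section's own list of expected intervention-related events.

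**Reach of the expected list.** Of the six seriousness criteria, four (death, threat to life, hospital admission, disability) correspond to classes listed as expected. What remains is (e), congenital anomaly, which has little application at age 65 and over, and (f), otherwise medically significant. Applied literally and alone, the related-and-unexpected test would let little through.

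**The case against.** The tempting stronger reading is that a related serious fall is never reported as an SAE. The document does not support it. The sentence on events expected at this age brings such a fall back in when it is related, and the DMEC/TSC paragraph shows the committee all treatment-related SAEs. The finding is a contradiction, not a settled exclusion.

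Other inferences also fail:

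- **That an unrelated event cannot be an SAE.** Criteria (a) to (f) contain no relatedness condition. The difficulty with unrelated SAEs lies only in the sentence restricting what is recorded.
- **That the steering section confines the committee to related and unexpected events.** For the proposed combined committee the stated role is inclusive, not exhaustive. The narrower wording concerns immediate notification to a separate DMEC, set up only if the funders refuse a single committee.
- **That the trial cannot describe harms, or that the committee is denied any view by arm.** Section 5.4.2 collects injuries, fractures, admissions, orthotic wear and exercise at the time of each fall, and fracture rate is a secondary outcome. Independent members may see unblinded data. The single final analysis in 5.4.4 concerns statistical analysis, not safety oversight.
- **That the second-appointment question conflicts with the recording rule.** Section 5.3.10 says of the podiatrists: "They will ask the participant if they have experienced any adverse events since their last appointment". They must ask before seriousness can be judged. What is unclear is what happens to a non-serious answer.

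It is also fair to say that this is a low-risk intervention and that limiting rapid REC reports to related and unexpected events is not in dispute. These points narrow the concern. They do not remove the conflicts shown for the three events, and outcome data on falls are no substitute for reporting ulcers, skin injury or admissions without a fall.

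**Conclusion.** The concern holds as a set of four conflicts:

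1. Non-serious events are both recorded and not recorded.
2. A related serious event of a listed type is both excluded from and included in SAE reporting.
3. SAE recording is limited to REC-reportable events, while the committee is promised unrelated SAEs.
4. The committee's immediate view differs between 5.3.13 and the separate-DMEC wording.

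The third depends on the assumption about REC-reportable SAEs, and the fourth matters in practice only if a separate DMEC is formed. The first two follow directly from 5.3.13.

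The effect cannot be put as a number, because what is lost depends on which sentence staff follow. The falls-rate analysis is untouched. What is at risk is the SAE status of related serious events of listed types and the count of non-serious harms other than falls. This should be corrected, since the conflict is in the protocol itself and is not detail that an analysis plan would supply.

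**What to change.** Rewrite 5.3.13 and the Independent Steering Committee section as one rule set with three separate parts: what is recorded, what the committee sees and when, and what goes to the REC within 15 days.

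- Keep the related-and-unexpected test for the 15-day REC report only, so that it limits neither recording nor committee review.
- Remove the sentence that non-serious events are not recorded, so that notified events, including the listed expected intervention events, are recorded.
- Give the committee the same remit in both sections, whether it is combined or separate.
- Show events meeting (a) to (f) by arm from sources common to both arms: reports to the trials unit and the 6 and 12 month questionnaires.
- Present events found at the second podiatry appointment or through the compliance questionnaires descriptively. Only the intervention arm attends that appointment, and Appendix 3 marks compliance data as intervention-only, so a comparison between arms from these sources would reflect unequal ascertainment.

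The cost is a wording change and modest extra data entry; no new visits are needed.

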**5.4 Data collection and analysis**

5.4.1 Quantitative data collection

Participant self-reported data will be collected at the following time points: at invitation, baseline (pre-randomisation/pre-assessment), monthly falls calendars and at six and 12 months post-randomisation/post-assessment for trial and cohort participants. Data on compliance to the intervention will be collected via questionnaire sent at 1, 3 6 and 12 months. For data collected post-randomisation/post assessment an option to complete the data on-line will be offered.

Follow-up questionnaires will be sent to participants in the post by the research team based at the University of York’s Trials Unit. Participants who provide an email address will be sent a pre-notification email, two weeks prior to the questionnaire being sent in the post. This email will alert participants that they will soon receive a follow-up questionnaire and that they can, if they prefer, complete the questionnaire on-line. Participants who do not return their follow-up questionnaire within two weeks will be sent up to two reminders, two weeks apart either by post, text or email. Members of the research team may also contact participants by telephone, post or email or text as per the participant’s preference regarding any queries they may have in relation to the follow-up questionnaires, exercise diaries or falls calendars. All participants will be sent an unconditional £5 with the 12 month questionnaire in recognition of their commitment to the study and to cover any expenses incurred in completing the questionnaires. When a participant has been lost to follow-up, their data will be included in the main analysis up to where they have been lost to follow-up.

Process data collected via the podiatrists will be collected at the patient’s initial and follow-up attendance to the podiatry clinic. Additional data will be collected if the participant attends additional trial appointments. Attendance to the podiatry clinic by the control participants and details of the treatment/advice given will be recorded.

5.4.2 Data collection for the primary outcome for the REFORM Trial

The primary outcome is the rate of falls (ie falls/person/time). A fall is defined as “an unexpected event in which the participant comes to rest on the ground, floor, or lower level”. [31] Data will be collected via participant self-reported falls calendars in the 12 months following randomisation. Participants will be asked to record if they had any fall or not for each day. Participants who do not return their falls calendar within one week of the due date will be telephoned by the YTU, and information collected from the patient over the phone. Participants will also be given the YTU free phone number to ring during office hours to report any fall they have as soon as possible after the fall. The YTU personnel will collect information including: details of the event ie date of event, cause/reason for fall, consequence of fall: superficial wound (bruising, sprain, cut, abrasions) or fractures and type of fracture, footwear worn whilst having the fall, hospital admissions, if the patient was wearing their orthotic at the time of falling or if they were undertaking the prescribed exercises, EQ5D. However, as we are also collecting falls data from the six and 12 month follow up questionnaires, these data will be used for those participants to do not return their monthly falls calendar.

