5.3.4. Primary outcome

The primary outcome is the rate of falls (i.e: falls/person/time) where a fall is defined as “an unexpected event in which the participant comes to rest on the ground, floor, or lower level”. [31]

5.3 5 Secondary outcome

Secondary outcomes are:

- Proportion of fallers
- Proportion of multiple fallers (more than two falls)
- Patient reported time to first fall during follow-up
- Health related quality of life as measured by the EQ-5D
- Short Falls Efficacy Scale
- Fear of falling
- Activity of Daily Living
- Fracture rate
- Health service utilisation
- Geriatric Depressions Scale

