5.4.5 Statistical analysis of the primary outcome

The number of falls per person will be analysed using a Poisson regression model adjusting for gender, age and history of falling to estimate the difference in falls rate between the groups. If there is over dispersion a negative binomial regression model adjusting for the same factors will be used [41] Point estimates and their associated 95% confidence intervals will be provided. For the main outcome a significance level of 0.05 will be used.

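### As worded, the falls calendar takes a yes/no entry per day, so on its own it records fall-days and may slightly undercount the falls that form the primary outcome

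*Protocol*

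**What the plan says.** Section 5.3.4 fixes the outcome: "The primary outcome is the rate of falls (i.e: falls/person/time". Section 5.4.2 repeats it. Section 5.4.5 models it as a count: "The number of falls per person will be analysed using a Poisson regression model", with a negative binomial model if the counts are overdispersed. Section 5.3.12 also uses the mean number of falls, to obtain a cost per fall averted.

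On collection, section 5.4.2 says "Data will be collected via participant self-reported falls calendars in the 12 months following randomisation", and describes the daily entry as follows: "Participants will be asked to record if they had any fall or not for each day". Three further routes appear in the same section:

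- Participants are given a freephone number "to ring during office hours to report any fall they have as soon as possible after the fall". Trial unit staff then take "details of the event ie date of event, cause/reason for fall, consequence of fall".
- A participant whose calendar is more than a week late is telephoned. The questions asked in that call are not specified.
- Falls are also asked about at 6 and 12 months, and "these data will be used for those participants to do not return their monthly falls calendar".

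Section 5.4.1 adds that the team may contact participants about queries on their calendars.

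The protocol does not say how a day with two or more falls is entered. Nor does it say how telephone reports and calendar entries are merged into one count.

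**The concern.** The outcome is a count of events, but the daily entry is binary. Summing yes/no entries over 12 months gives the number of days with a fall. This equals the number of falls except on days with more than one.

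Three things are at stake:

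- **Undercount.** Any loss concentrates in frequent fallers, who weigh most in a falls rate.
- **Consistency.** A participant who rings after each of two falls on one day can be credited with two. One who only marks the calendar is credited with one.
- **Recoverability.** This concerns what is collected. An analysis plan written later cannot restore a number that nobody asked for.

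**Working it through.** **Inputs from the protocol.** Control risk of falling is 50% in 12 months and target risk 40%; power is 80%, two-sided level 5%, loss to follow-up 10%, total 890 (section 5.3.6).

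**Inputs that are assumptions.** These are the falls rate per person, the dispersion k, the true rate ratio, and the share of falls that are second or later falls on the same day. The protocol gives none of them.

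**Step 1: the plan's own figure.** Two proportions, 50% versus 40%, need 388 per arm. Dividing by 0.90 gives 432 per arm, 864 in total. With a continuity correction the figures are 408, 454 and 908. The stated 890 lies between the two totals, and 400 evaluable per arm give power 0.81. The calculation rests on the proportion of fallers, which a yes/no daily entry captures, so the sample size is not affected.

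**Step 2: loss for one person with independent falls.** With λ falls a year, expected fall-days are 365 × (1 − exp(−λ/365)), and the share lost is 1 − fall-days/λ.

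| Falls per year | Share lost |
| --- | --- |
| 1 | 0.14% |
| 2 | 0.27% |
| 5 | 0.68% |
| 12 | 1.6% |
| 50 | 6.5% |

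**Step 3: loss over a trial arm.** Expanding the formula, the share lost is about E[λ²]/(2 × 365 × mean). For a negative binomial count with mean m and dispersion k, E[λ²] = m²(1 + 1/k), so the share lost is m(1 + 1/k)/730. The mean follows from P(no fall) = (1 + m/k)^(−k) = 0.5.

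- k = 0.5: m = 1.5, share lost = 1.5 × 3/730 = 0.62%.
- k = 1: m = 1.0, share lost = 1.0 × 2/730 = 0.27%.

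**Step 4: effect on the rate ratio under independence.** Take an assumed true ratio of 0.80 and k = 0.5. The intervention mean is 1.2 and its loss is 1.2 × 3/730 = 0.49%. The ratio is multiplied by (1 − 0.0049)/(1 − 0.0062) = 1.001, so 0.80 reads as 0.801.

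**Step 5: effect on falls averted in the same case.** Falls lost are 1.5 × 0.00616 = 0.0092 in controls and 1.2 × 0.00493 = 0.0059 in the intervention arm. The true difference of 0.300 falls per person reads as 0.300 − 0.0033 = 0.2967, about 1.1% too small.

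**Step 6: if falls cluster within a day.** Let q be the share of an arm's falls that are same-day repeats. The observed ratio is the true ratio × (1 − q intervention)/(1 − q control).

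| q control | q intervention | Factor | 0.80 reads as |
| --- | --- | --- | --- |
| 5% | 5% | 1.000 | 0.800 |
| 10% | 10% | 1.000 | 0.800 |
| 5% | 2% | 1.032 | 0.825 |
| 10% | 5% | 1.056 | 0.844 |

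The values of q are illustrations only.

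**The case against.** The strongest reply has four parts.

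- **The form is not shown.** The sentence in 5.4.2 may only mean that every day needs an entry, so that blanks are not read as fall-free days. The form may have room for a count. This is possible. If so, 5.4.2 misdescribes the form and needs correcting anyway.
- **Event-level capture exists.** The freephone report, the late-calendar call, the questionnaires and the query contact could each reveal a repeat fall. This stands in part. The freephone depends on the participant ringing in office hours, the call concerns late calendars only, the questionnaires substitute only where calendars are not returned, and a properly marked day raises no query. Someone who returns every calendar on time and does not ring is never described as being asked for a number.
- **The effect is negligible.** On the independence calculation it is, and that stands.
- **The outcomes behind the sample size are untouched.** Whether a person falls, and the day of the first fall, are captured in full by a yes/no entry. That stands.

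A reader might go further and infer three things that the protocol does not support.

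- **That the calendar cannot deliver the number of falls.** It delivers a count per person that is wrong only on days with more than one fall.
- **That the rate ratio is biased towards no effect by some 3% to 6%.** This needs same-day shares that differ between arms, and nothing in the protocol gives such shares or such a difference.
- **That a person whose only two falls came on one day is misclassified as a multiple faller or not.** Section 5.3.5 defines multiple fallers as having more than two falls, so on that definition the person is not one either way. The example works only on the contrast in 5.4.6, which sets multiple against single or non-fallers.

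**Conclusion.** The point holds as a modest measurement gap. The instrument described in 5.4.2 yields fall-days, the outcome and model are in falls, and the other routes do not reliably recover the difference.

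Its likely size is small: 0.3% to 0.6% of falls, a rate-ratio factor of about 1.001, and about 1% off the falls averted in the k = 0.5 case. These rest on independence over days, 50% of controls falling, k of 0.5 to 1 and, for the last two, a true ratio of 0.80. The loss is greater for very frequent fallers or with clustering within a day, by an amount that cannot be set from the protocol. Equal shares of same-day repeats in the two arms leave the rate ratio unchanged.

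It is still worth acting on, because asking for a number is a better measurement of the primary outcome at almost no cost.

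**What to change.** 1. Change 5.4.2 and the calendar to ask for the number of falls on each day (0, 1, 2 and so on), keeping an entry for fall-free days.
2. Ask the same question in the telephone call for late calendars.
3. State how telephone reports and calendar entries are combined into one count per person, by the same rule in both arms, so that one fall reported by two routes counts once and two falls on one day count twice.

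The cost is a wording change on a form already sent monthly, plus a short rule in the text. Asking about marked days on calendars already returned is optional. It would need some extra contact and staff time, although 5.4.1 already allows such contact.
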